### 4.2. SECONDARY OUTCOMES

Proportion achieving remission (PHQ9≤4) will be analysed using a mixed effect logistic regression model. If convergence fails, then week 6 and week 12 will be analysed as separate logistic regression models.

Secondary outcome measures will be analysed using analogous models to the primary outcome. This will include linear models adjusting for treatment group, baseline value of the dependent variable, and the stratification factors (BMI and PHQ-9).

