### 2. Inclusion Criteria

- Aged 18-65 years
- Have been diagnosed with depression
- Have had 2 or more antidepressant treatment trials of adequate dose and duration within the current depressive episode to which they did not fully respond. An adequate treatment trial is defined as at least 4 weeks of a medication at a minimum NICE-approved dose
- With a Patient Health Questionnaire-9 (PHQ-9) total score greater than or equal to 15 at baseline
- Able to understand and be willing to adhere to the demands of the study
- Provision of written informed consent
- Have access to a tablet/computer for online assessments, follow-ups with the registered dietitian, and able to attend appointments for assessments and treatment and adhere to study procedures
- Have both a fridge and a freezer at home
- Complete all baseline assessments

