### 1.4. OBJECTIVES AND OUTCOME MEASURES

Table 1 lists the primary and secondary outcome measures, an exploratory outcome measure, and mechanistic outcome measures. Table 1 corresponds to the primary, secondary and mechanistic outcome measures listed in Table 2 of the published protocol . Exploratory and process outcome measures are now listed in separate sections below.

| Table 1 Objectives and outcome measures |                                                              |                      |                             |
|------------------------------------------------|--------------------------------------------------------------|----------------------|-----------------------------|
|                                                | Objectives                                                   | Outcome Measures     | Time point(s)               |
| Primary                                 | Self-reported depression severity at post-treatment (week 6) | PHQ-9                | Weeks 6                     |
| Secondary                               | Self-reported depression severity during follow-ups          | PHQ-9                | Baseline, weeks 2, 4, 6, 12 |
| Secondary                               | Remission of depression                                      | PHQ-9 score $\leq 4$ | Baseline, weeks 6           |
| Secondary                               | Anxiety                                                      | GAD-7                | Baseline, weeks 2, 4, 6, 12 |
| Secondary                               | The inability to experience pleasure (i.e. anhedonia)        | SHAPS                | Baseline, week 6, 12        |
| Secondary                               | Cognitive functioning                                        | PDQ-5                | Baseline, week 6, 12        |
| Secondary                               | Health-related quality of life                               | SF-12                | Baseline, week 6, 12        |
| Secondary                               | Functional outcome                                           | WSAS                 | Baseline, week 6, 12        |

|                    |                                                                  |                                |                      |

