## 2.2. SAMPLE SIZE

We consider a 5-point difference in PHQ-9 total score (0-27 scale) to represent a minimum clinically important difference, as suggested by Lowe et al. This study reported that the SD of the change in PHQ-9 over 3 months as 5.8 and as 6.1 over 6 months. Assuming an SD of 6 over 6 weeks would suggest a standardised effect size of 0.83 in PHQ-9 to be clinically relevant. The sample size to test differences between groups at 90% power and at a type one error rate of 5% would be 64 (32 per group). A sample size of 100 participants will be recruited in case of 35% attrition/missing data. In simulations we confirmed that this sample size remains robust under scenarios such as unequal sizes of the strata used in minimisation. In actuality, recruitment was stopped when 88 people were randomised because it was clear that follow-up rates were substantially higher than predicted, meaning that we were on track to achieve more than 64 people contributing to the primary outcome and achieving sufficient power.

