## 4. PRIMARY ANALYSIS

### 4.1. PRIMARY OUTCOMES

The change in PHQ-9 scores from baseline to week 6 will be compared between groups. Initially, data will be plotted in the following tables. A linear contrast will be used to test the difference between groups in changes from baseline to week 6 in PHQ-9 scores. Two-tailed tests and a significance level of 0.05 will be used.

The statistical analysis of the primary outcome, effectiveness of the intervention for weight loss, will be carried out both on the basis of intention-to-treat (ITT) and per-protocol (PP). For the ITT analysis, participants will be analysed according to their allocated intervention group. For the per-protocol analysis, we will include participants who, in at least 5 out of the 6 follow-up calls, were rated by health coaches as adhering to the diet at levels of "Completely/Every Day" or "Mostly/Most of the Days".

In both cases, a linear mixed effect model that includes treatment group, time (categorical) and their interaction as fixed effects, and individual subjects as random effects will be fit using PHQ-9 at all available assessments. We will include stratification variables (BMI values and PHQ-9) as continuous variables.

The primary and secondary treatment effects will be given by the interaction between timepoint and treatment. We will present the outcome in the original units of the scale and calculate Cohen's d.

Normality of residuals will be checked graphically. If there are substantial violations from normality in the primary analysis then a non-parametric *p*-value will be calculated by permutation testing. For binary outcomes, we will use analogous generalised linear models.

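### The SAP gives remission different time points in two places and lets model convergence decide which odds ratio is reported

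*Combined protocol and SAP*

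**What the plan says.** - **Time points.** In SAP 1.4, Table 1, the remission row gives its time points as "Baseline, weeks 6". Every other secondary row includes week 12.
- **First-choice model.** SAP 4.2: "Proportion achieving remission (PHQ9≤4) will be analysed using a mixed effect logistic regression model". The visits entering this model are not named.
- **Fallback.** SAP 4.2 continues: "If convergence fails, then week 6 and week 12 will be analysed as separate logistic regression models". Week 12 is therefore treated as a remission time point.
- **Effect definition.** SAP 4.1: "The primary and secondary treatment effects will be given by the interaction between timepoint and treatment", and "For binary outcomes, we will use analogous generalised linear models". No summary measure is named for remission, whether odds ratio, risk difference or other.
- **Entry criterion.** Protocol Section F, Inclusion Criteria: "With a Patient Health Questionnaire-9 (PHQ-9) total score greater than or equal to 15 at baseline".
- **Size.** SAP 2.2: "recruitment was stopped when 88 people were randomised".

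Neither section says what counts as failed convergence or which covariates the fallback for remission carries. The outline of secondary outcomes in protocol Section E does not list remission.

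**The concern.** There are two separate problems.

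First, a reader cannot tell whether week-12 remission is a pre-specified outcome. The outcome table says no and the analysis section says yes.

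Second, the two models in 4.2 do not estimate the same thing. A random-intercept logistic model compares the odds of remission under the two diets for a person with a given value of the random effect. A logistic model fitted to one visit compares odds averaged over those person effects. The conditional odds ratio lies further from 1 whenever both the between-person variance and the treatment effect are non-zero. A numerical event in the fitting software would thus decide which is published, and a report that says only that an odds ratio was estimated would not tell readers which they have. Anyone pooling or comparing remission results could be misled about the size of the effect.

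**Working it through.** **Plan's own figure.** None exists for remission: no expected rate, odds ratio, random-effect variance or correlation. The sample-size figures in SAP 2.2 concern mean PHQ-9 and do not bear on this. The only remission rate in the documents is a background 13% in protocol Section E, which is not a design assumption.

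**Step 1, time points side by side.** Table 1 has baseline and week 6. SAP 4.2 has week 6 and week 12. SAP 11, which lists outcomes added since the published protocol, mentions only the learning task at week 12, so it does not explain the difference.

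**Step 2, why the fallback could be triggered.** Entry needs PHQ-9 ≥15 and remission needs ≤4, so the baseline remission count is 0 in both arms by design. SAP 4.1 fits the primary model to all available assessments with a treatment-by-time interaction and asks for analogous models for binary outcomes. Carried over literally to remission, this gives an outcome visit with zero events in each arm. That is complete separation at that visit, with its log odds running to minus infinity. If only Table 1's visits are used, baseline carries no information and each person contributes one informative binary observation. The random-intercept variance is then not identified.

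**Step 3, how far apart the two odds ratios are.** Assumed inputs: remission proportions p0 and p1 at week 6, and latent within-person correlation ρ.

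- Single-visit OR = [p1/(1−p1)] / [p0/(1−p0)]. For 10% vs 25%: (0.25/0.75)/(0.10/0.90) = 3.00. For 13% vs 26%: (0.26/0.74)/(0.13/0.87) = 2.35. For 13% vs 16%: (0.16/0.84)/(0.13/0.87) = 1.27.
- Random-intercept SD: s = √[ρ/(1−ρ) × π²/3], giving 1.19, 1.81 and 2.77 at ρ = 0.3, 0.5 and 0.7.
- For each arm, solve E[expit(a + sZ)] = p for a, with Z standard normal (80-point Gauss-Hermite quadrature). Conditional OR = exp(a1 − a0).

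Example, 10% vs 25% at ρ = 0.5: a0 = −3.237 and a1 = −1.686. The difference is 1.552 before rounding, and exp(1.552) = 4.72.

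| Assumed remission | Single-visit OR | Conditional OR, ρ = 0.3 | ρ = 0.5 | ρ = 0.7 |
|---|---|---|---|---|
| 10% vs 25% | 3.00 | 3.70 (×1.23) | 4.72 (×1.57) | 7.45 (×2.48) |
| 13% vs 26% | 2.35 | 2.80 (×1.19) | 3.42 (×1.45) | 4.93 (×2.10) |
| 13% vs 16% | 1.27 | 1.33 (×1.04) | 1.40 (×1.10) | 1.55 (×1.21) |

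**Step 4, does the conclusion change?** Trials of 88 people (44 per arm) were simulated with two or four post-baseline visits, about 120 trials per scenario, unadjusted and without missing data. The scenarios were 10% vs 25%, 15% vs 30% and 15% vs 15% at latent normal correlation 0.5, plus 15% vs 30% at 0.7. Trials with a zero cell were excluded. The random-intercept and week-6-only models agreed on significance at 0.05 in 94–100% of trials, with z-statistics correlated at 0.99 or above. Between 112 and 120 of 120 trials per scenario gave a usable mixed fit once baseline was left out.

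**The case against.** Four points can fairly be made against this.

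- **Both routes are written down in advance.** If the mixed model fails there is no second odds ratio to choose from. This stands: the plan does not leave a free choice to the analyst. What remains is an undefined trigger and an unnamed summary measure.
- **The models test the same null.** The conditional log odds ratio and its standard error grow together, so significance hardly moves. This stands, as step 4 shows.
- **Week 12 is probably just missing from a table row.** Protocol Section E plans to follow outcomes to 12 weeks, and the other secondary rows include it. That is a plausible explanation, but the SAP does not give it, so the mismatch still needs correcting.
- **Few remissions alone need not break the mixed model.** With post-baseline visits only, it was usable in nearly all simulated trials. This stands too. The convergence risk comes mainly from including baseline, which the SAP does not rule out.

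A reader might infer three stronger things that the documents do not support. One is that the reported effect could double as a matter of course. Doubling needs a latent correlation of about 0.6–0.7 or more together with a single-visit odds ratio of about 2.3 or more, and the documents give neither. Another is that a headline result is at risk. SAP 4.2 speaks of a proportion and never names an odds ratio, and the main result is PHQ-9 at week 6. The third is that the added visit creates a multiplicity defect specific to remission. SAP 4.7 declines correction for all comparisons, and testing both visits remains possible under the fix below.

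**Conclusion.** The point holds in a limited form. Table 1 and 4.2 contradict each other on week 12. Separately, 4.2 allows convergence to determine whether the odds ratio is conditional on the subject effect or averaged over it. Under the assumed rates and correlations of step 3, the conditional odds ratio exceeds the single-visit one by roughly 20% to 150% when the effect is substantial (10% vs 25% or 13% vs 26%), and by 4% to 21% near the null (13% vs 16%). The consequence is for the size and meaning of the reported effect, not materially for its significance.

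Two qualifications apply. The odds ratio as summary is inferred from the model type. And the fallback averages only over the random effect: if BMI and baseline PHQ-9 are kept in it, its odds ratio is still conditional on those covariates. This is a secondary outcome, and the correction is worth making because it is cheap.

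**What to change.** Amend SAP Table 1 and 4.2 together:

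1. State that remission at week 6 is the secondary endpoint, and add week 12 to the table labelled as a follow-up result.
2. State that baseline is not an outcome visit for remission.
3. Name one reported measure, whichever model is fitted: the standardised (marginal) risk difference and odds ratio at week 6, adjusted for baseline PHQ-9 and BMI. Report week 12 in the same way.
4. If a single-visit logistic model is used, state in 4.2 that missing PHQ-9 scores are multiply imputed from all visits before remission is derived, so that the analysis does not default to complete cases.
5. If the mixed model is kept as first choice, define convergence failure.

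The cost is SAP wording and a little more analysis work for the standardisation and imputation. A single-visit model does not itself borrow from other visits; the imputation in item 4 recovers this under a missing-at-random assumption, which SAP 4.5 already makes for the primary analysis. If the remission analysis has already been run, the change can be reported as a deviation, as SAP 1.1 provides.

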### 4.3. EXPLORATORY AND DESCRIPTIVE OUTCOMES

The following exploratory outcomes will be reported descriptively. To facilitate interpretation, we propose to analyse weight change, rather than BMI change in the protocol given those two

are exactly equivalent. In the protocol, dietary adherence was listed as an exploratory outcome, but here we classify it as a process outcome (Section 4.4 below).

| Objectives         | Objectives          | Outcome Measures | Time point(s)         |
|--------------------|---------------------|------------------|-----------------------|
| Exploratory | Change in weight    | Self-measured    | Baseline, weeks 6, 12 |
| Exploratory | Alcohol use         | AUDIT            | Baseline, week 12*    |
| Exploratory | Smoking             | Self-reported    | Baseline, week 6, 12  |
| Exploratory | Illicit drug use    | Self-reported    | Baseline, week 6, 12  |
| Exploratory | Being off work sick | Self-reported    | Baseline, week 6, 12  |

\* For alcohol, week 6 is omitted here, since at week 6 abstinence from alcohol is a component of adherence to the ketogenic diet.

#### 4.4. PROCESS OUTCOMES

The following outcomes will be presented descriptively

| Objectives                                | Outcome Measures                                                                                                                                                                                                                                                                 | Time point(s)          |
|-------------------------------------------|----------------------------------------------------------------------------------------------------------------------------------------------------------------------------------------------------------------------------------------------------------------------------------|------------------------|
| Intervention engagement            | Proportion of sessions attended (Numbers of attended/6)                                                                                                                                                                                                                          | Baseline, week 6       |
| Dietary adherence score            | The percentage of health coaches selecting 'Completely/Every Day' or 'Mostly/Most of the Days' when assessing participants' adherence to the diet.                                                                                                                               | Weeks 1, 2, 3, 4, 5, 6 |
| Ketone levels                      | 
 
- the percentage of achieving ketosis level of 1.5 mmol/L and above
 
- the percentage of achieving ketosis level of 4 mmol/L and above
 
- the percentage of achieving ketosis level of median mmol/L and above
 
 | Weeks 1, 2, 3, 4, 5, 6 |
| Diet adherence after intervention  | Self-reported adherence to KD at each time point "Are you still following the diet that the dietitian advised you to follow?"                                                                                                                                                    | Week 12                |
| Satisfaction with the intervention | Proportion of diet and study satisfaction (e.g. I have enjoyed the food I have eaten over the past six weeks, how was your experience of the diet and support you got)                                                                                                           | Weeks 6                |

## 4.5. HANDLING MISSING DATA

The primary analysis is a mixed effects model using available case analysis. This is valid under a missing at random assumption (MAR).

Sensitivity analyses will include assumptions that those with missing data have either severe depression (PHQ-9 score 20), worst case depression (PHQ-9 score 27), unchanged score with baseline observation carried forward, unchanged score with last observation carried forward, or have achieved remission (PHQ-9 score 4).

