| 5. | Saliva/stool samples                      | We will send participants a sample kit for collecting salivary cortisol and stool samples. Collection and packaging the stool sample will take less than 5 minutes plus time taken to post the sample in the pre-packaged and paid for posting pack. Salivary samples are taken in the first hour of the designated day and take about 2 minutes to collect and deal with each sample, which is collected by putting a dental roll in the mouth and extruding it into a plastic container. Participants will be able to do other things during collection but not eat. Samples will be collected on waking, and at 30, 45, and 60 minutes after waking. The samples will be sent back to the laboratory in a pre-addressed and stamped padded envelope. |

Note: Postcode will be converted to an index of multiple deprivation score and the demographic variables will be presented by group at baseline for descriptive purposes only.

After all baseline assessments are complete, participants will be allocated by minimisation 1:1 to the KD group or control group. A researcher will embed a non-deterministic algorithm in the Redcap database. This algorithm aims to produce treatment groups balanced for important prognostic factors by minimising on the following variables (as below). Only after eligibility and consent is confirmed will the database reveal the allocation. Investigators delivering the intervention will not be blinded, but the outcome is collected blind (by self-report), and those involved in analysing the outcome data will be blinded to allocation.

- BMI (less than 30 kg/m^2 vs. 30+ kg/m^2)
- Depression severity (PHQ-9 score: 15-19 [moderately severe] vs. 20-27 [severe])

All follow-up is done online and without trial staff and will therefore not be subject to observation bias. Following randomisation, participants will be given information and advice for their respective group.

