
3. Repeat main analysis with analysis restricted to (a) those with maximum of one missing observations (b) those with maximum of two missing observations

Complete case analysis will be used as the primary analysis if the proportion of missing data is below 5%. We will conduct a sensitivity analysis to explore reasons for missingness and determine appropriate handling of missing data. The following approaches may be applied based on the missing data: single imputation (e.g., last observation carried forward) and full information maximum likelihood estimation. Intention-to-treat analysis using baseline or last observation carried forward (LOCF) are recommended for parallel group randomised trials by CONSORT guidelines since they provide a full report of any deviation of the intervention and includes every participant who enrolled in the study and completed baseline measures, regardless of whether they completed the intervention. ITT also gives an unbiased estimate of the treatment effect. If data are missing not at random (MNAR) for our continuous dependent outcome variables, full information maximum likelihood estimation will be used because it is more compatible between the imputation and analysis models compared to multiple imputation.

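### The missing-data sensitivity analyses probe departures from MAR only narrowly: with equal dropout the fixed-value scenarios share one estimate, and none varies an arm-specific departure

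*Combined protocol and SAP*

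**What the plan says.** The primary analysis in SAP 4.1 is a linear mixed model for PHQ-9 at every available assessment, with arm, categorical time and their interaction. SAP 4.5 states that it is valid under MAR. The sensitivity set follows: "Sensitivity analyses will include assumptions that those with missing data have either severe depression (PHQ-9 score 20), worst case depression (PHQ-9 score 27"), baseline observation carried forward (BOCF), last observation carried forward (LOCF), and remission at a score of 4. Each rule applies to anyone with missing data, whichever the arm.

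Protocol Section J, item 4, says that robustness to MAR will be tested. It lists two scenarios (all missing are severe; all missing have no depression) and two restrictions (at most one, or at most two, missing observations). It adds: "If data are missing not at random (MNAR) for our continuous dependent outcome variables, full information maximum likelihood estimation will be used". It also says: "Complete case analysis will be used as the primary analysis if the proportion of missing data is below 5" per cent. SAP 4.5 contains neither of these last two provisions. Neither document has a delta-adjusted, reference-based or tipping-point analysis.

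**The concern.** The protocol describes the trial as open-label. The outcome is self-reported, and one arm follows a demanding diet. A plausible failure of MAR is arm-specific: people lost from the KD arm may fare worse than their earlier scores predict, while those lost from the control arm do not. A useful sensitivity analysis lets that gap vary and shows how large it must be before the conclusion changes.

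The planned set looks like five separate tests. If three or four of them share one point estimate, agreement among them says less about robustness than it seems to. The method that the protocol reserves for MNAR data does not relax MAR. A report could then claim robustness over several scenarios after testing essentially one size of departure. The 5% rule also leaves two candidate primary analyses, depending on which document is followed.

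**Working it through.** **Inputs from the documents.** Design difference 5 points: "We consider a 5-point difference in PHQ-9 total score (0-27 scale) to represent a minimum clinically important difference". SD 6: "Assuming an SD of 6 over 6 weeks would suggest a standardised effect size of 0.83 in PHQ-9 to be clinically relevant". Two-sided 5% (SAP 4.1), 90% power, 1:1 allocation, 88 randomised (SAP 2.2).

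**Assumptions.** 44 per arm; completer week-6 means of 10 (KD) and 15 (control); SD 6 for the week-6 score; missing fractions as shown. The documents give none of these. With 88 randomised and at least 64 evaluable, overall missingness would be at most 1 - 64/88 = 27%.

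**The plan's own figure.** 5/6 = 0.83. The normal approximation gives 2 × (1.96 + 1.282)² × 36/25 = 30.3, so 31 per arm; the noncentral-t calculation gives 32 per arm (power 0.907), the plan's 64. Then 64/0.65 = 98.5, so 99 against the stated 100. The figure reproduces.

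**Step 1: equal dropout.** Let d be the completer difference (control minus KD, positive favours KD), p the missing fraction in each arm, and c the imputed constant. The difference is (1-p)d + p(c - c) = (1-p)d, so c cancels. With d = 5:

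| p | Estimate for c = 4, 20 and 27 | z for c = 4 / 20 / 27 |
|---|---|---|
| 10% | 4.50 | 3.36 / 3.42 / 2.93 |
| 20% | 4.00 | 2.92 / 3.01 / 2.36 |
| 27% | 3.65 | 2.65 / 2.76 / 2.06 |
| 35% | 3.25 | 2.37 / 2.49 / 1.79 |

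The identity covers the point estimate only. Standard errors differ (at 20%: 1.37, 1.33 and 1.70), and at 35% significance differs too. A simulation of the planned mixed model with 20% missing at week 6 in both arms gave differences in favour of KD of 4.00 for all three constants, 4.02 for BOCF, 4.63 for LOCF and 5.05 for the MAR analysis.

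**Step 2: what the constants assume.** If MAR predicts roughly the completer means, imputing 20 shifts KD dropouts by 20 - 10 = +10 and control dropouts by 20 - 15 = +5. For 27 the shifts are +17 and +12; for 4 they are -6 and -11. The net KD penalty is 5 each time, which is d itself.

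**Step 3: unequal dropout.** With 27% missing in KD and 10% in control, the difference is 0.90 × 15 - 0.73 × 10 + c(0.10 - 0.27) = 6.2 - 0.17c, which gives 5.52, 2.80 and 1.61 for c = 4, 20 and 27. The constants now spread widely (simulated model: 5.59, 2.68 and 1.41). The spread is driven by the dropout imbalance, not by a chosen arm-specific departure.

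**Step 4: a KD-only shift.** Add δ to the imputed KD values after MAR imputation. With equal dropout the estimate is d - pδ. Taking SE = 6√(2/(44(1-p))), significance is lost at δ = (d - 1.96 SE)/p:

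| p | 1.96 SE | δ for d = 5 | δ for d = 4 | δ for d = 3 |
|---|---|---|---|---|
| 10% | 2.643 | 23.6 | 13.6 | 3.6 |
| 20% | 2.803 | 11.0 | 6.0 | 1.0 |
| 27% | 2.935 | 7.6 | 3.9 | 0.2 |
| 35% | 3.110 | 5.4 | 2.5 | not significant at δ = 0 |

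The SE here is that of an unadjusted comparison, held fixed. Shifted values also widen the spread, which lowers the larger entries. At p = 10% and d = 5, solving 5 - 0.1δ = 1.96√(1.348² + 0.09δ²/44) gives δ of about 18.8. With a KD mean of 10 on a 0-27 scale the average shift cannot exceed 17, so that cell stays out of reach either way.

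**Step 5: the protocol sentences.** Full information maximum likelihood and the likelihood-based mixed model both rest on MAR. Using the former because data are thought to be MNAR repeats the primary assumption. The 5% rule names complete cases as primary, whereas SAP 4.5 uses the available-case mixed model without any threshold.

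**The case against.** A reader might infer that the planned checks cannot test departures from MAR at all. The documents do not support that. Imputing 4, 20, 27 or the baseline score is itself a departure from MAR and moves the estimate from 5 to 4 at 20% missing. LOCF gives a different value because it uses each person's own earlier scores.

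A reader might also infer that no scenario looks in the direction of the likely bias. Step 2 shows otherwise: each constant already penalises KD dropouts by the whole observed difference. The fair criticism is that only one size of penalty is examined. Even that needs equal dropout, which no document states, and loss from a demanding diet could well be unequal.

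Several features limit the problem. Stopping the diet does not count as leaving the study (protocol Section G.5). Non-responders are phoned for the PHQ-9 (Section G.2), with a voucher for that alone (Section G.7). Scores at weeks 2 and 4 inform the model, and SAP 2.2 reports better follow-up than predicted. These reduce missing data without removing them.

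The maximum-likelihood sentence and the 5% rule appear only in the protocol, which calls its statistical text an outline ahead of a detailed SAP. The risk to the reported analysis from those two sentences is therefore small. All of these objections stand, and they narrow the point. They do not supply an analysis in which the arm-specific departure varies.

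**Conclusion.** The point holds in limited form. With equal dropout, the three constants, and nearly BOCF, are one scenario for the point estimate: a net KD penalty equal to the completer difference. Standard errors and p-values still differ, LOCF differs, and the constants spread when dropout is unequal. No planned analysis varies the size of an arm-specific departure. The protocol's MNAR sentence is technically wrong, and its 5% rule conflicts with the SAP.

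The consequence depends on the result. At the 5-point design difference with about 10% missing it is small, because the tipping shift is about 24 points under the simple approximation. It is material for smaller effects or more missing data: 11.0 points at d = 5 with 20% missing, and 3.6 at d = 3 with 10% missing. The claim that missing data could decide the trial would rest on an assumed effect of about 3 points, just above the significance threshold of 2.64 to 2.68 (normal or t quantile) at 10% missing. The documents do not establish such an effect. All these sizes rest on the assumed 44 per arm, SD, means and equal dropout.

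**What to change.** Keep the scenarios in SAP 4.5 and add one analysis. Multiply impute week-6 PHQ-9 under MAR within arm, then add delta from 0 to 10 points (for example in steps of 2) to the imputed KD values only, and separately to both arms. Report the delta at which the 95% confidence interval first includes 0, or that none in the range does so. The both-arms version moves the estimate only if dropout is unequal, so report missing numbers by arm beside it. SAP section 10 says that code and output for the primary outcome have been reviewed, so label the addition post hoc if results have been seen.

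In protocol Section J, delete or correct the sentence that offers full information maximum likelihood for MNAR data. State that the SAP mixed model is primary whatever the missing fraction, which removes the 5% switch.

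The cost is a paragraph of SAP text, a short Stata routine and one extra sensitivity table.
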